## Methods

The current study is a two-armed RCT study with a crossover design. Both groups will receive treatment. Group A is scheduled for V-CBT within one week of randomization and group B with a delayed onset 3 months after randomization. See Fig. 1 flow diagram.

**Fig. 1 Fig1:**
[figure not shown]
Flow diagram for the procedure

### Enrolment

Participants are recruited between 2 to 3 months after the whiplash injury. This is done through the National Patient Register that provides names and addresses on patients who fulfil the ICD-10 diagnose code for a whiplash injury (distorsio columnae cervicalis) and are situated in the region Zealand were the study intervention takes place. Monthly, a research assistant identifies all new whiplash cases in the region Zealand. Potential participants are contacted by letter and invited to participate in the study. All potential participants are asked to rate their average level of pain on a numerical pain rating scales (NRS) ranging from 0 (no pain) to 10 (worst possible pain). Participants who volunteer to participate and experience pain levels corresponding to ≥ 4 on average are further screened by a brief telephone interview. During the telephone screening the participants are orally informed of the project and asked additional questions regarding experienced daily life difficulties in relation to their whiplash trauma. Participants who fulfil the outlined criteria for inclusion (for details, look beneath) and accept participation are referred to one of two trained, clinical psychologist for their first counselling session. Participants are informed that they are allowed to bring a relative to the first consultation. Written informed consent will be obtained from all participants prior to entry into the study. Before the first session and randomization, they receive a letter with additional written information about the study, a statement of consent and the baseline questionnaire. At the first consultation and before randomization, all participants and their relatives are thoroughly informed about the randomization procedure, the intervention, and expected outcome of the study. Participants, who at any given time in the process, do not wish to participate, are not questioned further about this decision.

### Participants

All participants are between the age of 18 and 65-years old and are diagnosed with WAD grade I-II [23]. At 3-months post injury, they are experiencing disability in at least one important life domain (≥5 on the pain disability index) and moderate levels of pain (average pain intensity ≥ 4 on the NRS scale). Also, they have to meet at least one of the psychological risk criteria: elevated levels of pain catastrophizing, fear-avoidance beliefs, symptoms of anxiety and/or depression, and posttraumatic stress symptoms). Clinically relevant cut-off score criteria are based on previous studies [21, 24, 25]. Criteria of exclusion is treatment for other damages sustained in connection with the whiplash trauma, psychiatric disorders, active abuses of alcohol, drugs, or medication, ongoing rehabilitation or other treatment for pain besides physiotherapy and pharmacological treatment, and non-Danish speaking.

### Randomization and blinding

Patients are randomized by random permuted blocks of 4 to 8 by the study statistician at University of Southern Denmark. Randomization is consecutively numbered in sealed opaque envelopes. Patients will randomly be allocated to one of two treatment groups (A or B) in a crossover design with both groups receiving the V-CBT intervention, however with a delayed onset for group B. Group A is scheduled for V-CBT within one week of randomization and group B with a delayed onset of 3-months after randomization. Measurements of effect are carried out at baseline before randomization (3 months post-injury), post-treatment/wait-list (3 months post randomization), and at follow-up (9 months post randomization/12 months post-injury). At all time points patients are asked which potential additional treatment they have received. The clinical psychologists are not blinded to which intervention the patients receive. However, at the point of analysis, the two groups will be coded as X and Y in order to blind the researcher who will conduct analysis.

### Intervention: value-based cognitive-behavioural therapy

The V-CBT is a manualized program specifically tailored for prevention of disability and psychological distress after whiplash injuries [26]. The theoretical foundation of the program is learning theory as outlined by Fordyce [27], and value-based behaviour change strategies as described in contextual cognitive-behavioural therapy [19, 28, 29]. The V-CBT program has a common goal with acceptance and commitment therapy (ACT), to improve daily life functioning and facilitate behaving in accordance with personal values and life-goals. Although, the V-CBT program facilitates behavioural changes according to personal values and life goals, the program does not directly target psychological flexibility by the use of acceptance and mindfulness strategies. The first session of the program is dedicated to assessing personal values and daily life goals. Values and life goals are assessed by an interview based on the patient’s response on the pain disability index, on which affected life domains are reported.

The V-CBT program is rooted in learning theory [27] reflected in the primary focus on imaginal- and in-vivo exposure strategies. For these reasons we have chosen to name the program Value-based Cognitive behavioural therapy. Within the framework of learning theory it is emphasized how negative reinforcement can result in avoidance behaviour and limitations of activity and how events only loosely associated with earlier aversive events may come to serve as cues and conditioned negative reinforces resulting in more avoidance behaviour and activity restrictions. Combining the principles of learning theory with value-based actions, the primary goal of the program is functional restoration of everyday life activities and not necessary symptom eradication. Two trained clinical psychologists deliver the intervention. The psychologists have several years of experience delivering CBT and receive bi-weekly supervision. The program consists of 10 weekly one-hour individual sessions. For a program description, see Table 1.

**Table 1 Tab1:** Content of the value-based cognitive behavioral therapy program

Session and topic		Aims	Homework/techniques
1-2	Introduction.	To introduce the program. Discuss affected life domains and values. Give insight into the difference between active vs. passive coping.	Discuss important values with the family or a close friend. Complete value template.
	Affected life domains.		
	Values and life goals.		
	Week-plan.		Activity registration.
3	Pain theory and activity engagement according to values.	To introduce pain models and the bio-psycho-social perspective. Discuss values and activity engagement. Setting new short- and long-term value-based goals. Discuss daily activities and make an exercise plan.	Complete week plan according to planned activities.
			Establish a workout routine.
4	“Road-block” therapy.	To discuss psychosocial barriers for fulfilling goals. Introduce the concept negative reinforcement and the power of habits. Introduce the cognitive ABC model. Setting new realistic measureable goals.	Work with barriers, cognitive, emotional or practical.
	Negative reinforcement.		
			Complete week plan according to planned activities.
			Workout.
5	Unfulfilled expectations.	To discuss expectations to oneself and how unfulfilled expectations can affect mood and behaviour resulting in maladaptive coping.	Complete plan B and set realistic goals for the day.
	Having a plan B.		
			Complete week plan according to planned activities.
		Learn to work out a plan B.	
			Workout.
6	The energy balance and psychological barriers for activity engagement.	Learn to conserve “energy”, prioritise in activities.	Identify energy consuming activities vs. activities that increases energy.
		Discuss psychological barriers for activity engagement.	
	Adjust goals.		
			Use the ABC model.
		Discuss life values and adjust goals accordingly.	Complete week plan according to planned activities.
			Workout.
7	Psychological barriers.	To work more in depth with individual psychological distress and barriers for activity engagement, for instance depressive symptoms, PTSD, or pain catastrophizing.	Use the ABC model.
			Complete week plan according to planned activities.
			Workout.
8	Psychological barriers.	To work more in depth with individual psychological distress and barriers for activity engagement. Work out an exposure hierarchy of feared activities.	In vivo exposure.
			Complete week plan according to planned activities.
			Workout.
9	Activity engagement and return to work or relevant activities.	Discuss return to work or relevant activities. Work with fear-avoidance beliefs and catastrophizing.	In vivo exposure of work related activities.
			Complete week plan according to planned activities.
			Workout.
10	Long-term goals and values.	To discuss progress and values. Set long-term goals and work out a plan for setbacks and maintenance of progress.	Discuss long-term goals and plan with a close relative or friend.

Before the first session, all patients receive a 14-min psycho-educational video produced with the purpose of reassurance after acute and subacute whiplash injury. The video includes education in the physiology of a cervical strain, possible symptoms and prognosis, coping strategies, and encouragement to gradually maintain pre-injury activity.

The main components of the V-CBT program are: 1) Education in pain theory and active coping, 2) unlearning fear-conditioned movement restrictions, 3) gradual increase in activity, 4) daily program of movement or excises, 5) change of dysfunctional thoughts and catastrophizing and focused treatment of mild PTSD-symptoms by imaginal and in-vivo exposure, and 6) development of a plan on how to return to work or relevant activities. The patients are expected to participate actively between sessions by doing homework. Weekly goals regarding resumption of daily activities or tasks are set throughout the program.

### Measures

#### Primary outcome

The primary measure of outcome is disability as measured with the Pain Disability Index (PDI) [30]. The PDI measures how pain interferes with daily life activities within 7 different domains. The 7 domains are rated from 0 (no disability) to 10 (worst disability). The scale shows good reliability and validity [31].

#### Secondary outcomes

Neck pain intensity and disability is measured with the Neck Disability Index (NDI) [25]. The NDI measures within 10 domains how neck pain affects the ability to handle daily life activities such as personal care, lifting, reading, work, driving, sleeping, recreational activities, pain intensity, concentration, and headache. The total score range from 0 (no disability) to 100 (total disability).

Pain is also measured on four numerical pain rating scales (NRS) ranging from 0 (no pain) to 10 (worst possible pain). Patients mark their answers on each scale corresponding to their pain now, highest level of pain, lowest level of pain, and finally average pain over the past week (NRS) [32].

Fear of re-injury due to movement is measured with Tampa Scale for Kinesiophobia (TSK) [33]. TSK is a 17-item scale assessing fear of movement on a 4-point likert scale ranging from 17 to 68 with higher scores indicating higher levels of kinesiophobia. The scale is commonly used in various chronic pain samples and has good construct and predictive validity [34].

Catastrophic thinking related to pain is measured with the Pain Catastrophizing Scale (PCS) [35]. The PCS ask participants to reflect on past painful experiences and to indicate the degree to which they experienced each of 13 thoughts or feelings when experiencing pain on a five-point Likert scale with (0 = not at all, 4 = all the time). The PCS has been shown to have high internal consistency and to be associated with heightened pain and disability [35]. A high score indicates high level of pain catastrophizing.

To assess the level of anxiety and depressive symptoms, the Hospital Anxiety and Depression Scale is used (HADS) [36]. The scale consists of 14 items, seven relating to anxiety (HADS-A) and seven to depression (HADS-D) with responses ranging from 0 (no symptoms) to 3 (maximum impairment). Internal consistency is high and the scale has proven sensitive for detecting clinical changes [37].

PTSD symptomatology is measured with the PTSD-8 [24]. The scale is a brief version of The Harvard Trauma Questionnaire part IV [38]. The PTSD-8 consists of 8 items on a four-point Likert scale (1 = not at all, 4 = very often). The items relate to the three core clusters in PTSD in DSM-IV: avoidance (2 items), intrusion (4 items), and hyperarousal (2 items). The scale has proven good psychometric properties in various trauma samples including whiplash injured [24].

### Sample size and statistical analysis

To our knowledge no similar studies have been conducted. For this reason, the power calculation is estimated according to the earlier studies using CBT and acceptance-based strategies with functional restoration and activity engagement as their primary goal. From these earlier results, a moderate effect size is to be expected (η_p_^2^ = 0.25) [19, 20]. By putting the level of significance at 5 %, the power at 80 %, and the expected dropout at 9 months post-randomization to be 10 %, it is calculated that there should be 40 patients in each group (A & B).

The primary and secondary outcomes measured for both groups at baseline before randomization (3 months post-injury), 3 months post-randomization, and 9 months post randomization (12 months post-injury) will be analysed using linear mixed-effects models (random coefficient models and multilevel models). With the mixed effects model approach all available data will be used and intention-to-treat analyses applied.

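### The sample size of 40 per group follows neither from the stated ηp² = 0.25, which is a very large effect, nor from the word moderate attached to it

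*Protocol article*

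**What the plan says.** Under *Sample size and statistical analysis*, the protocol article bases its power calculation on earlier studies of CBT and acceptance-based treatment: "From these earlier results, a moderate effect size is to be expected", given as ηp² = 0.25. The other inputs follow: "By putting the level of significance at 5" per cent, "the power at 80" per cent, and "the expected dropout at 9 months post-randomization to be 10" per cent. The conclusion is that "it is calculated that there should be 40 patients in each group (A & B").

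The paragraph does not give the sidedness, the test, a standard deviation, a PDI difference or a within-patient correlation. The outcomes "will be analysed using linear mixed-effects models (random coefficient models and multilevel models") over baseline, 3 months and 9 months after randomization. *Methods* describes immediate treatment (group A) against treatment delayed by 3 months (group B). The two groups therefore differ as treated versus untreated only up to the 3-month visit.

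**The concern.** The paragraph gives every ingredient of a conventional calculation and its result, so it can be checked as it stands. Two things do not fit.

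- **Label against value.** Usual benchmarks put a medium effect at ηp² about 0.06 (f = 0.25, d = 0.5) and a large one at about 0.14 (f = 0.40, d = 0.8). A value of 0.25 lies well beyond large.
- **Inputs against result.** The stated value leads to far fewer than 40 per group. The conventional moderate value, tested in the simplest way, leads to far more.

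What is at stake is how the result can be read. If V-CBT shows no significant benefit over the wait-list, a reader will want to know which size of effect the trial could reasonably have missed. The paragraph gives two incompatible answers, and the number enrolled matches neither.

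**Working it through.** **Inputs from the article:** ηp² = 0.25; 5% significance; 80% power; 10% dropout at 9 months; 40 per group. **Assumptions:** two-sided test, equal allocation, and an unadjusted comparison of two means at one visit unless stated otherwise. Power is from the noncentral t distribution with noncentrality d√(n/2) and 2n − 2 degrees of freedom, where n is the number per group.

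**1. Attempt to reproduce 40 from the stated value.**
- f = √(0.25/0.75) = 0.577, and d = 2f = 1.155.
- n = 12 gives 77.1% power and n = 13 gives 80.6%, so 13 evaluable per group are needed.
- Dropout: 13/0.9 = 14.4, so 15 enrolled per group.
- At 40 × 0.9 = 36 evaluable per group, power is 99.8%. At 40 it is 99.9%.
- One-sided testing lowers the requirement further.
- Repeated-measures F tests at f = 0.577 (between-group or group-by-time, 2 or 3 visits, correlation 0 to 0.7) need 6 to 24 evaluable patients in total.

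None of the variants tried at ηp² = 0.25 that keep 5% and 80% returns 40 per group.

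**2. Take the word moderate instead.**
- d = 0.5, f = 0.25, ηp² = 0.0625/1.0625 = 0.059.
- n = 63 gives 79.5% and n = 64 gives 80.1%, so 64 evaluable per group are needed.
- Dropout: 64/0.9 = 71.1, so 72 enrolled per group.

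**3. Look for a route to about 80 in total.** The closest match among the variants tried reads 0.25 as f rather than ηp², in a between-group F test that averages three visits with correlation 0.3.
- The noncentrality is f²·N·m/(1 + (m − 1)ρ), with N the total, m the visits and ρ the correlation. For N = 70 it is 0.0625 × 70 × 3/1.6 = 8.20, and 70 is the smallest even total that reaches 80%.
- Dropout: 70/0.9 = 77.8, so 78 enrolled, or 39 per group.

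The article states neither that test nor that correlation. The average would also include baseline, before any treatment, and the 9-month visit, after group B has been treated. It is not the V-CBT versus wait-list contrast of the first hypothesis.

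**4. What 40 per group delivers.** The 10% dropout is stated for 9 months and none is given for 3 months. The range from 36 (the 9-month figure) to 40 (no loss) is therefore shown.

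| | 36 per group | 40 per group |
|---|---|---|
| d with 80% power, unadjusted | 0.67 | 0.63 |
| the same as ηp² = (d/2)²/(1 + (d/2)²) | 0.10 | 0.09 |
| power at d = 0.5, unadjusted | 55% | 60% |
| power at d = 0.5, baseline-adjusted, assumed r = 0.5 | 68% | 72% |

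The adjusted row replaces d by d/√(1 − r²) = 0.5/√0.75 = 0.577 and loses one degree of freedom. At 36 per group, adjusted power is 59% at r = 0.3 and 74% at r = 0.6. It reaches 80% at r of about 0.67 (about 0.62 at 40 per group).

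**The case against.** The strongest defence is that the planned analysis is a mixed model over three visits, not a t test at one visit, and that such a model can give 80% power for a moderate effect with 80 patients. This partly stands. Baseline adjustment reaches 80% at d = 0.5 if the correlation is high enough. With f = 0.25 under the usual repeated-measures formulas, a three-visit group-by-time test needs only 54, 38 or 28 evaluable patients in total at correlations of 0, 0.3 and 0.5. That f is not the same quantity as d = 0.5 at one visit, and all of this rests on a correlation the article does not give. It shows that any shortfall in power depends on the test. It does not reconcile the printed inputs with 40.

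A second defence is that ηp² = 0.25 may come from an adjusted model in the cited studies, so that d = 1.15 overstates the effect in raw standard deviations. That is possible. With an assumed baseline correlation of 0.7, the raw effect would be 1.155 × √(1 − 0.49) = 0.82. An unadjusted test would then need about 2 × (1.960 + 0.842)²/0.825² = 23.1, so 24 per group by the normal approximation, or 27 after dropout. The mismatch remains.

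Third, an article condenses the full protocol, so the missing test, visit and sidedness are not faults in themselves. I agree and do not count them. The point is that figures which are printed disagree with each other, and no unseen document can make them agree.

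A reader might go further and infer that the trial is underpowered, with little better than an even chance of detecting its target effect. The article does not support that. The 55% applies to one unadjusted test at 36 per group and to d = 0.5, whereas at the printed value the power exceeds 99%. A reader might also infer that f = 0.25 was mistyped as ηp². That would explain the word moderate, but it cannot be shown from the text.

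**Conclusion.** The point holds in this limited form: the sample-size statement is wrong as written. ηp² = 0.25 is not a conventional moderate effect. With the stated 5%, 80% and 10% dropout it leads to about 15 enrolled per group rather than 40. A conventional moderate effect, in an unadjusted single-visit comparison, leads to 72. The effect for which 40 per group gives 80% power, unadjusted, lies between the two: d of about 0.63 to 0.67, or ηp² of about 0.09 to 0.10.

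These figures assume two-sided testing and d = 2f for two equal groups. That ηp² = 0.25 leads to far fewer than 40 per group also held in the one-sided and repeated-measures variants tried. The figure of 72 is more sensitive and falls with baseline adjustment. Whether the trial has adequate power for the effect its authors had in mind cannot be settled from the article.

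**What to change.** Keep 40 per group, remove the pairing of moderate with ηp² = 0.25, and state what the size delivers for the PDI at a named visit with a named test. For example:

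> With 40 patients per group, and 36 to 40 evaluable, a two-sided 5% unadjusted comparison of PDI at 3 months after randomization has 80% power for a standardised difference of about 0.67 to 0.63 (ηp² about 0.10 to 0.09). Power for a difference of 0.5 is 55 to 60%, or about 68 to 72% with baseline adjustment if the baseline correlation is 0.5 (assumed). The 10% dropout refers to 9 months.

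Tie the power statement to the V-CBT versus wait-list contrast before group B is treated. When naming the visit, reconcile it with *Aims and hypotheses*, which places the wait-list comparison at 6 months post-randomization, whereas measurements are planned at 3 and 9 months. If the authors have an estimate of the baseline correlation, it should replace the assumed 0.5.

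The cost is one rewritten paragraph and a less favourable headline figure. No patients are added, and neither the design nor the analysis changes.

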### Ethics statements

The study is presented and approved of The Regional Scientific Ethical Committee for Southern Denmark (J.nr. S-20130103) and the Danish Data Protection Agency. All procedures in the study are in accordance with the second declaration of Helsinki. The intervention is an additional offer to treatment as usual, and everybody is free to say no to participation.

## Discussion

The primary objective of the present study is to test whether the specifically tailored V-CBT program is able to prevent the development of persistent disability, pain, and psychological distress if delivered within the first three months after a whiplash injury. In particular, early identification and targeting of fear-avoidance beliefs, pain catastrophizing, and symptoms of PTSD seem to be of importance.

In contrast to symptom reduction, aiming to improve functioning and activity engagement in patients has shown promising results [18, 19, 29]. In particular, the combination of exposure and value-based strategies for functional restoration may be important. Also, addressing PTSD symptomatology seems essential in relation to functional restoration [17]. Based on learning theory [9, 27], maladaptive pain behaviours may develop within the fist weeks after an injury, why early intervention may prevent this maladaptive pattern. Indeed, this is indicated by Adams and Colleagues [20], finding their intervention most effective when delivered within three months after the whiplash injury. However, research has yet to determine in a RCT study whether targeting these early risk factors will prevent long-term disability and psychological distress. Also, it is important to gain knowledge whether there exists a 3-months window for intervention, as indicated by longitudinal cohort studies of recovery after whiplash injury [7].

Whiplash injury is the most common injury after traffic accidents and represents a major societal and personal problem. For this reason, if effective, the intervention program will have significant importance for both patients and the society. Moreover, the program can easy be implement in already established pain clinics around the country. In the present study no health economic analyses are planned. However, recently a study by Kemani and colleagues [39] showed that acceptance and commitment therapy for longstanding pain was more cost-effective than an active control treatment. The present study could be strengthened by a register study of the long-term health-economic effects of the V-CBT program.

The study can be subjected to some challenges. It may be difficult to recruit patients in the sub-acute phase since most patients are informed that their symptoms will disappear by themself. Also, most patients hold a traditional biomedical view of the injury, why an early psychological intervention seldom is their first choice of treatment. Also, dropout could be significant due to remission or change in priorities during the intervention. In order to prevent this, motivational factors are kept in mind during the process of treatment. Patients enrolled in the study are contacted by phone before onset of treatment in order to remind them and motivate them for coming. Also, at follow up, patients are reminded personally. Finally, it is important to keep in mind, that although the intervention may prove effective in preventing the development of chronic WAD, the intervention is aimed at the particular subgroup of WAD with a psychological risk profile. Not all WAD are associated with pain related anxiety, and avoidance behaviour needing treatment [40].
